# Investigational Product

## OJS plus SMS

| ***Ojeok-san*** |  |
| --- | --- |
| Atractylodis Rhizoma | 0.95 |
| Ephedrae Herba | 0.2 |
| Citri Unshius Pericarpium | 0.4 |
| Magnoliae Cortex | 0.08 |
| Platycodonis Radix | 0.43 |
| Aurantii Immaturus Fructus | 0.31 |
| Angelicae Gigantis Radix | 0.37 |
| Zingiberis Rhizoma | 0.22 |
| Paeoniae Radix | 0.27 |
| Poria Sclerotium | 0.02 |
| Cnidii Rhizoma | 0.3 |
| Angelicae Dahuricae Radix | 0.31 |
| Pinelliae Tuber | 0.22 |
| Cinnamomi Cortex | 0.04 |
| Glycyrrhizae Radix et Rhizoma | 0.2 |
| Zingiberis Rhizoma Recens | 0.03 |
| Total | 4.35 |
| ***Saengmaek-san*** |  |
| Liriopis Tuber | 0.75 |
| Ginseng Radix | 0.30 |
| Schisandrae Fructus | 0.36 |
| Total | 1.41 |

## Placebo

Placebos do not contain any of the active ingredients, OJS or SMS, and are composed of starch, lactose, and coloring and flavoring agents.

# Procedure

## Timetable

|  | **STUDY PERIOD** | | | | | |
| --- | --- | --- | --- | --- | --- | --- |
|  | **Enrolment** | **Allocation** | **Post-allocation** | | | **Follow-up** |
| **VISIT** | ***1*** | **2** | ***3*** | ***4*** | ***5*** | ***6*** |
| **TIMEPOINT** | ***-2~1 week*** | **0** | ***2 weeks ± 3days*** | ***4 weeks ± 3days*** | ***6 weeks ± 3days*** | ***8 weeks ± 3days*** |
| **ENROLMENT:** |  |  |  |  |  |  |
| Eligibility screen | X |  |  |  |  |  |
| Informed consent | X |  |  |  |  |  |
| Demographics | X |  |  |  |  |  |
| Medical and  treatment history | X |  |  |  |  |  |
| Physical examination | X |  |  |  |  |  |
| Vital sign | X | X | X | X | X | X |
| Chest X-ray | X | X | X | X | X | X |
| Pulmonary Function Test | X |  |  |  |  |  |
| FeNO | X |  |  |  |  |  |
| Nasal Endoscopy | X |  |  |  |  |  |
| PNS x-ray (if needed) | X |  |  |  |  |  |
| EKG | X |  |  |  |  |  |
| Laboratory tests | X |  |  |  | X |  |
| Pregnancy Test | X |  |  |  |  |  |
| Allocation |  | X |  |  |  |  |
| **INTERVENTIONS:** |  |  |  |  |  |  |
| OJS plus SMS |  |  |  |  |  |  |
| Placebo |  |  |  |  |  |  |
| **ASSESSMENTS:** |  |  |  |  |  |  |
| Cough Symptom Score | X | X | X | X | X | X |
| Cough VAS | X | X | X | X | X | X |
| LCQ-K |  | X | X | X | X | X |
| GERDQ |  | X | X | X | X | X |
| HARQ |  | X | X | X | X | X |
| Pattern Identification for Chronic Cough Questionnaire | X | X |  |  |  |  |
| Pattern Identification for GERD |  | X |  |  |  |  |
| EQ-5D-5L |  | X | X | X | X | X |
| Abdominal Examination |  | X |  |  |  |  |
| WPAI:SHP |  | X | X | X | X | X |
| Adverse events |  | X | X | X | X | X |
| Compliance test |  |  | X | X | X |  |

## Efficacy Outcome Measures

### Primary Efficacy Outcome

#### Cough symptom score (Cough diary)

The CDS is a subjective cough score questionnaire that assesses the severity and frequency of cough on five scales (0 to 4) during the daytime and nighttime ^18^. The cough severity scale is divided into 0: none, 1: slight, 2: mild, 3: moderate, and 4: severe, whereas the cough frequency ranges between 0 (none), 1 (infrequent/occasional), 2 (several times), 3 (many times), and 4 (all the time). Each of the daytime and nighttime scores is calculated by adding the score of cough severity and cough frequency, with a maximum score of 8; the total CDS is an averaged score of daytime and nighttime CDS. All participants will be instructed to record their CDS twice a day: daytime score assessing symptoms occurring from 8am to 8pm and nighttime score from 8pm to 8am. At every visit, a Cough Diary will be given to each participant to record their symptoms until the next visit, and the average score between visits will be used as the outcome to evaluate the efficacy of OJS plus SMS compared with the placebo.

The primary outcome of this trial is the change in CDS between baseline (pre-drug) and week 6 (post-drug) in the OJS plus SMS group compared to the placebo group. CDS was chosen as the primary outcome measure, as a subjective cough score is the most frequently used outcome in clinical trials related to cough ^19^ and was also the primary outcome in our pilot trial showing significant differences between OJS plus SMS and placebo.

### Secondary efficacy outcome

#### Cough VAS (Cough diary)

The cough VAS is another cough score outcome widely used to assess acute or chronic cough ^20 21^. It is also highly responsible for changes in cough severity, making it easy to compare therapeutic effects in clinical trials ^22^. The participants were asked to mark the severity of cough on the line with a calibration of 0 to 100 mm, with 0 indicating ‘no cough’ and 10 indicating ‘unbearable cough.’ The distance between zero and the marked point will be measured using the cough visual analog scale score. Participants will be instructed to record the cough VAS daily in the given cough diary for the next 2 weeks, and the average score will be used as the outcome.

#### Leicester Cough Questionnaire-Korean (LCQ-K)

The LCQ-K, which consists of 19 items, is a quality of life (QoL) questionnaire specified for cough symptoms. Each item ranges from 1 to 7, with higher scores indicating a better quality of life and is divided into three domains: physical, mental, and social ^23^. Previous studies have demonstrated a relationship between the LCQ score and the severity of cough, and it is also recommended by the European Respiratory Society as a QoL outcome for the impact of cough in patients with chronic cough ^24^. The validated Korean version of the LCQ will be used in the trials at each visit ^25^.

#### Gastroesophageal reflux disease questionnaire (GERDQ)

The GERDQ is a validated patient-report questionnaire for diagnosis and management of GERD ^26^. It includes six items related to symptoms such as heartburn, regurgitation, upper stomach pain, nausea, night sleep disturbance, and the need for additional medication. Each item is graded from 0 to 3 according to the frequency of symptoms in the past 1 week, with a higher score indicating more severe GERD-related symptoms. As the GERDQ is not only used for assessing changes in treatment outcomes but also for diagnosing GERD, it will be useful to identify GERD severity in patients enrolled in our trial as none, mild, moderate, or severe ^27^. Therefore, it can be used to compare the efficacy of OJS plus SMS in symptomatic and non-symptomatic patients with GERD.

#### Hull Airway Reflux (hypersensitivity) Questionnaire (HARQ)

The HARQ is designed to measure cough hypersensitivity and contains 14 items graded from 0 to 5, with a maximum score of 70 points. Higher scores indicated higher sensitivity of the airway ^28^. As cough hypersensitivity is highly related to chronic cough and represents a distinct clinical entity, the HARQ was used to assess patients with GERC in this trial.

#### Pattern Identification for Chronic Cough Questionnaire (PICCQ)

The Pattern Identification for Chronic Cough Questionnaire will be assessed at baseline to compare the differences in efficacy by pattern identification. Based on the pattern identification for chronic cough, participants will be classified into one of five patterns: cold wind, phlegm turbidity, fire heat, lung deficiency, or kidney yang deficiency ^30^. These pattern identifications are the diagnostic and treatment criteria used in Korean Medicine to determine appropriate therapies for each patient. Thus, it is important to assess the relationship between these patterns and the therapeutic efficacy of OJS plus SMS.

#### Pattern Identification for GERD

Pattern identification for GERD will also be performed in all participants at baseline. We will investigate the distribution of pattern identification in patients with GERC and the pattern identification that best responds to OJS plus SMS. Pattern identification of GERD includes stagnation of Liver Qi, stomach yin deficiency, spleen–stomach weakness, and spleen-stomach dampness-heat. The questionnaire contains 40 items, of which 23 are self-report items and 8 are assessed by a Korean Medicine Doctor ^31^.

## Safety Outcomes

1. Adverse Events
2. vital signs (blood pressure, body temperature, pulse rate, and respiratory rate)
3. EKG
4. Laboratory tests

For the safety outcomes, vital signs (blood pressure, body temperature, pulse rate, and respiratory rate), adverse events, and laboratory test will be evaluated during the trial period. At every visit, vital signs and adverse events will be assessed, and laboratory tests will be conducted before and after drug administration. Liver function tests (aspartate aminotransferase, alanine aminotransferase, alkaline phosphatase, gamma-glutamyl transferase, bilirubin, and protein/albumin), renal function tests (blood urea nitrogen and creatinine), electrolyte content (sodium, potassium, and chloride), blood coagulation tests (prothrombin time and activated partial thromboplastin time), and complete blood count will be performed. Adverse events will be collected by asking participants whether any unfavorable and unintended signs, symptoms, or diseases presented after taking the investigational medicine. These will then be assessed for severity and causality of investigational drugs, and investigators will follow up until the adverse events end.

## Economic evaluation

We will conduct an economic evaluation from the healthcare system and societal perspective over 8 weeks of the trial period in parallel with a randomized controlled trial (RCT). We will estimate cost-utility as the primary economic endpoint and cost-effectiveness as a secondary economic endpoint of OJS plus SMS compared with placebo. Utility data will be collected from trial outcomes of the EQ-5D-5L, a health-related quality of life questionnaire assessed at every visit, and quality-adjusted life years (QALYs) will be calculated to estimate the incremental cost-utility ratio. Effectiveness data will also be obtained from the efficacy outcomes in the main RCT, including the CDS, cough VAS, LCQ-K, GERDQ, and HARQ scores, which will be used to estimate the incremental cost-effectiveness ratio. Cost data will be obtained in terms of medical and non-medical costs (transportation, time, and nursing care costs) and productivity loss costs from institutional data, a specially developed questionnaire for cost, and data from Statistics Korea, if needed. Additionally, sensitivity analysis will be performed on possible variables using one-way sensitivity analysis and probability sensitivity analysis with representative values and the distribution of variables.

# Statistical analysis

Statistical analysis will be performed by an independent statistician using SAS Analytics Pro software and significance will be accepted at an α-level of 0.05 in a two-sided test. For all data analyses, full analysis (FAS) set will be the primary analysis set in this trial, and a per-protocol (PP) set will be performed as an additional analysis. In this trial, the FAS set included all randomly assigned participants who had been evaluated for efficacy at least once after the administration of the investigational medicine. PP sets were defined as participants who completed the trial without violating the protocol, with compliance lower than 75%, taking prohibited medications, or presenting with serious adverse events. Continuous variables are presented as means and 95% confidence intervals and categorical variables as frequencies and percentages.

For primary efficacy analysis, the changes in CDS between baseline and week 6 of OJS plus SMS compared with placebo will be evaluated using a mixed-effect model repeated measure (MMRM), with each group and visit set as fixed effects and participants as random effects. Secondary efficacy analysis, comparing cough VAS, LCQ-K, GERDQ, HARQ, and EQ-5D-5L evaluated at each visit point with baseline between groups, will also be performed using MMRM. The analysis of the changes in each efficacy outcome within the group will be performed using a paired t-test or Wilcoxon signed-rank test, depending on its normality. For missing values, a multiple imputation will be performed. Additionally, to analyze the trends of CDS over time compared with the baseline, RM-ANOVA will be conducted, and Dunnett’s procedure (based on the baseline) will be used as a multiple comparison correction. A safety analysis will be conducted to compare the number of adverse events between groups using Fisher’s exact test.

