# Trial Design

## Procedure

This study is a randomized, double-blind, placebo-controlled, parallel, multi-center, investigator-initiated clinical trial to assess the efficacy, safety, and economic value of OJS plus SMS compared to placebo in patients with GERC. The trial will be conducted at five hospitals in South Korea: Kyung Hee University Korean Medicine Hospital, Gangdong Kyung Hee University Korean Medicine Hospital, Daejeon University Daejeon Korean Medicine Hospital, Pusan National University Korean Medicine Hospital, and Catholic Kwangdong University International St. Mary's Hospital. After participants voluntarily signed a written informed consent, they will be screened for eligibility assessment, and those who meet the inclusion criteria will be enrolled for the next 8 weeks of the trial period (Fig.1). A total of 138 participants will be enrolled in this study from January, 2024. Participants will be allocated to either the OJS plus SMS group or the placebo group in a 1:1 ratio and will be asked to administer the investigational medicine three times a day for 6 weeks. For the evaluation of efficacy, safety, and economic assessments, participants will visit every 2 weeks until the last follow-up visit on week 8.

[figure not shown]

<임상시험 진행 흐름>

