# Dropout and Early termination criteria

At any time during the clinical trial, participants can voluntarily withdraw from the clinical trial. Additionally, anyone who meets any of the following conditions will be dropped out from the trial at the discretion of investigators:

1. found to violate the inclusion and exclusion criteria after screening visit,
2. in the case where the participant requests discontinuation of the trial or refuses the treatment due to unsatisfactory treatment effects during the trial period,
3. in the case where the participant cannot be tracked during the trial period,
4. when it is judged by investigators that trial participation is no longer possible due to an adverse reaction or a concomitant disease,
5. in the case of taking prohibited drugs that may affect the trial result without the instruction of investigators during the trial period,
6. when it is judged that the effect evaluation of the clinical trial is not appropriate because the overall compliance with the investigational products is less than 70% in YGJ and PWS groups,
7. when the participant violates the trial plan, and it is difficult for the participant to continue the trial, and
8. when investigators judged that the progress of the clinical trial is no more appropriate.

In principle, this clinical trial is finalized when the registration of the planned number of participants is completed and the completeness of the collected data is secured. However, in the following cases, this clinical trial can be discontinued: (1) when the harmfulness of the supplied investigational products is found, (2) if moderate or severe adverse events judged to be related to investigational products occur in more than 25% of all participants, and (3) in the case when the targeted participants are not registered even though a sufficient recruitment period has been given.

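### The single per-protocol definition has no week-6 cut-off, so events in the off-drug weeks 6-8 can remove participants whose primary result is already complete

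*Protocol*

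**What the plan says.** The Statistical analysis section of the protocol sets the roles of the two populations: "full analysis (FAS) set will be the primary analysis set in this trial, and a per-protocol (PP) set will be performed as an additional analysis". It then defines the second one: "PP sets were defined as participants who completed the trial without violating the protocol". The same sentence goes on to list compliance below 75%, prohibited drugs and, last, serious adverse events. The sentence is awkward. I read its opening negative as governing the whole list, so that low compliance, prohibited drugs and serious adverse events are all reasons for exclusion. No item carries a date limit, and no separate PP set is given for any endpoint.

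The timing comes from elsewhere in the protocol:

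- Length of the trial (Procedure): "those who meet the inclusion criteria will be enrolled for the next 8 weeks of the trial period", and "participants will visit every 2 weeks until the last follow-up visit on week 8".
- Dosing (Procedure): participants "will be asked to administer the investigational medicine three times a day for 6 weeks".
- Primary endpoint (Cough symptom score): "The primary outcome of this trial is the change in CDS between baseline (pre-drug) and week 6 (post-drug"). The score for a visit is the diary average since the previous visit.
- Dropout item 5 (Dropout and Early termination criteria) concerns prohibited drugs and spans the whole trial: "in the case of taking prohibited drugs that may affect the trial result without the instruction of investigators during the trial period".

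**The concern.** The primary value is fixed at Visit 5, yet membership of the PP set stays open until Visit 6, about two weeks after dosing stops. Nothing that happens after Visit 5 can change a week-6 diary average, but it can decide whether that average is used.

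This matters because the later events need not be random. A participant still coughing at week 6 may have more reason to resume medication, or less reason to return. If that tendency follows week-6 response, excluding these participants selects on the outcome being analysed. If it also differs between arms, the PP treatment difference is biased. The direction depends on which arm loses more poor responders. If losses are equal and unrelated to response, there is no bias, only wasted data. What is at stake is the supportive analysis that readers will take as the effect in adherent participants.

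**Working it through.** **1. Timing, set side by side**

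| Item | Closes at | Protocol section |
|---|---|---|
| Dosing | Week 6 | Procedure |
| Compliance checks | Visit 5 (done at Visits 3, 4 and 5 only) | Timetable |
| Primary CDS value | Visit 5 (diary from Visit 4 to Visit 5) | Cough symptom score |
| Trial completion | Visit 6, week 8 | Procedure, Timetable |
| PP conditions | No limit stated | Statistical analysis |

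The gap is 8 − 6 = 2 weeks, subject to visit windows of ±3 days. Adherence and the primary outcome are both fully known at the start of it.

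**2. The plan's own sample size**

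Inputs from the Sample size section: difference 0.75, SD 1.4, two-sided alpha 0.05, power 0.80, dropout 20%.

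n per group = 2 × (1.960 + 0.842)² × 1.4² / 0.75² = 54.7, rounded up to 55. Then 55 / (1 − 0.20) = 68.75, rounded up to 69, or 138 in total. This matches the plan. The 20% is not split by time, so it does not show how many losses fall in weeks 6-8.

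**3. Discarded data (loss rates assumed)**

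(a) Suppose the whole 20% is lost by week 6. Then 69 × 0.80 = 55.2 per group have a week-6 result, and a further share is removed for later events:

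| Removed for weeks 6-8 | PP per group | Power |
|---|---|---|
| 0% | 55.2 | 0.804 |
| 2% | 54.1 | 0.796 |
| 5% | 52.4 | 0.783 |
| 10% | 49.7 | 0.761 |

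(b) Suppose instead that 20% is the total loss by week 8, and that 2, 5 or 10 percentage points of it fall in weeks 6-8. A PP set closed at week 6 would keep 56.6, 58.7 or 62.1 per group (power 0.813, 0.827 or 0.847). Under the current wording it keeps 55.2 (0.804).

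**4. Possible bias (loss rates and correlation assumed)**

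Let a fraction f be lost because a latent propensity exceeds a threshold, and let that propensity have correlation rho with a poor week-6 change. The mean of those retained shifts by

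SD × rho × φ(z) / (1 − f), with z = Φ⁻¹(1 − f).

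- f = 0.15: 1.4 × 0.274 = 0.384, times rho.
- f = 0.05: 1.4 × 0.1086 = 0.152, times rho.
- Difference between arms: 0.384 − 0.152 = 0.232, times rho.

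With 15% lost on placebo and 5% on active, the PP difference shrinks by 0.070 at rho = 0.3 (9% of 0.75) and by 0.116 at rho = 0.5 (15%). With the rates exchanged, it grows by the same amounts.

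**The case against.** The strongest reply is that little depends on this set. The FAS is primary and needs only one efficacy evaluation after dosing, so these participants' week-6 results stay in the primary analysis. The sample size does not rest on the PP set either. This stands, and it limits the point to a minor one.

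Second, one completer-based PP set is a common and simple choice. It also serves the secondary outcomes and CDS trends that run to week 8, where completing the trial is a sensible condition. That stands too: the definition is not wrong in itself, but it lacks a cut-off for the week-6 endpoint.

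Third, dating deviations is often left to the SAP, and the Statistical analysis section does not name the visit at which the trial counts as completed. The week-8 reading comes from the Procedure section, and an SAP could narrow it. This carries some weight. But the protocol does not leave the matter open: it states a rule, and on its plain reading that rule conditions a week-6 analysis on later events.

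Fourth, a reader might infer that anyone who restarts a reflux or cough medicine at week 7 is certainly excluded. The protocol does not go that far. The drug classes it lists are pre-entry exclusions, and it gives no list of drugs prohibited during the study. Dropout item 5 is limited to drugs that could influence the result and were taken without investigator instruction, and it is applied at the investigator's discretion. A missed Visit 6 or a serious adverse event in weeks 6-8 is the clearer case.

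Finally, selection on response before week 6 (for example, withdrawal for lack of effect) is inherent in any PP set, and a Visit 5 cut-off does not remove it.

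**Conclusion.** The point holds as a minor defect in a supportive analysis. On the wording given, events after the primary endpoint is complete can remove valid week-6 results from the PP set. This wastes data. It biases the PP estimate only if those events depend on week-6 response and differ by arm, and the direction could be either way.

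The size cannot be derived from the protocol. The shift of 0.07 to 0.12 points rests wholly on assumed losses of 15% and 5% and an assumed latent correlation of 0.3 to 0.5. A reader might push the same formula to rho = 1 and quote 0.23 points, or 31% of 0.75. That should not be used: it means that exactly the worst responders leave. Nor can it be read as a correlation with the binary event of being lost, which for a normal outcome cannot exceed φ(z)/√(f(1 − f)), about 0.65 at f = 0.15 and 0.47 at f = 0.05. Nor should a loss fraction be applied to 55 per group as though it were established: 55 is already net of the planned 20%, and if that 20% covers all 8 weeks, losses in weeks 6-8 would be counted twice. A reader might also infer that the trial's main conclusion is at risk. It is not, because the FAS analysis does not use this rule.

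**What to change.** Add one sentence to the Statistical analysis section, before unblinding. For the week-6 primary endpoint, PP status should depend on completing Visit 5 with a week-6 CDS value and on deviations dated up to and including Visit 5. Keep the full-trial completion condition for PP analyses of week-8 results. Settling it before unblinding matters, because a cut-off chosen afterwards could be chosen to suit the result.

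The change needs no additional participants or assessments and leaves the dropout and other clinical rules as they are. It has two costs. Deviations and medication use must be dated relative to Visit 5; the Timetable has no concomitant-medication row, so the sponsor should confirm that the eCRF captures those dates. The report will also carry two PP populations instead of one.

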## Sample size

1. **Sample Size**

| OJS plus SMS group | Placebo group | Total |
| --- | --- | --- |
| 69 | 69 | 138 |

1. **Rationale**

Based on our previous study results, we calculated a sample size of 138 (69 participants for each group) for this trial (16). The calculation was conducted to test the difference in the change in CDS from baseline (week 0) to post-dosing of OJS plus SMS (week 6) compared with the placebo. In our preliminary clinical trial, the mean difference between the two groups was found to be 0.75 and the standard deviation was 1.4. We assumed the power to detect the difference to be 0.8, the two-sided significance level to be 0.05, and a dropout rate of 20% to determine the sample size.

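### The primary MMRM of change in CDS omits baseline CDS, a covariate the trial already collects, and so gives up precision at no saving

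*Protocol*

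**What the plan says.** The Statistical analysis section of the Protocol names both the primary response and the model. It states that "the changes in CDS between baseline and week 6 of OJS plus SMS compared with placebo will be evaluated using a mixed-effect model" for repeated measures (MMRM), "with each group and visit set as fixed effects and participants as random effects". The secondary scores are to be analysed with the same type of model. No other section adds a covariate.

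The Timetable schedules the Cough Symptom Score at all six visits, including visit 1 (screening) and visit 2 (week 0, allocation). Participants' eligibility sets no minimum CDS. Randomization and Blinding describes 1:1 block randomization and names no stratification factor.

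The Sample size section is built on the same contrast: "The calculation was conducted to test the difference in the change in CDS from baseline (week 0) to post-dosing". Its inputs are that "the mean difference between the two groups was found to be 0.75 and the standard deviation was 1.4", with power 0.8, "the two-sided significance level to be 0.05" and 20% dropout.

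**The concern.** Change from baseline is usually correlated with baseline. Participants who start high tend to fall towards the mean, and those who start low on a 0 to 8 score have little room to improve. A model of change without baseline leaves that explainable variation in the error term. It also fixes the weight on a chance baseline difference at exactly one, whatever the data say.

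The Background calls the trial confirmatory. It is sized at 80% power on a difference and SD taken from a pilot, so it has no reserve if the true effect is smaller. What is at stake is precision, and how far the result depends on which arm happened to start with the worse cough.

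**Working it through.** **Inputs.** From Sample size: difference 0.75, SD 1.4, power 0.8, two-sided 0.05, dropout 20%. I read 1.4 as the SD of change, because the calculation concerns a difference in change. The baseline-to-week-6 correlation r and the separate SDs at baseline and week 6 are not in the Protocol and are assumed below.

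**1. The plan's own figure.** n per arm = 2 × (1.960 + 0.842)² × 1.4² / 0.75² = 54.7, rounded up to 55. With dropout, 55 / 0.8 = 68.75, rounded up to 69 per arm, or 138 in total. This matches exactly. The power of an unadjusted two-sample t-test at 55 per arm is 79.5% (80.2% by the normal approximation).

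**2. Precision under equal variances.** Let s be the SD of CDS at each time point.
- Variance of change: 2s²(1 − r)
- Variance after adjustment for baseline: s²(1 − r²)
- Ratio, adjusted to unadjusted: (1 + r)/2
- Adjusted SD: 1.4 × √((1 + r)/2)

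| Assumed r | Variance ratio | Adjusted SD | t-test power, 55 per arm |
|---|---|---|---|
| unadjusted | 1 | 1.40 | 79.5% |
| 0.3 | 0.65 | 1.13 | 93.2% |
| 0.5 | 0.75 | 1.21 | 89.5% |
| 0.7 | 0.85 | 1.29 | 85.5% |
| 0.9 | 0.95 | 1.36 | 81.5% |

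**3. Unequal variances.** With k the ratio of the week-6 SD to the baseline SD, the variance ratio becomes k²(1 − r²)/(1 + k² − 2rk). For an assumed k = 1.3:
- r = 0.5: 1.69 × 0.75 / (2.69 − 1.30) = 0.912, a fall of 9% instead of 25%.
- r = 0.7: 1.69 × 0.51 / (2.69 − 1.82) = 0.991, a fall of 1% instead of 15%.

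With k below 1 the gain is larger than in the table. For k = 0.8 and r = 0.5 the ratio is 0.64 × 0.75 / (1.64 − 0.80) = 0.571.

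**4. Chance imbalance, equal variances.** Subtracting baseline removes the whole baseline difference, whereas only r times it is expected to persist at week 6. The remainder is (1 − r) times the imbalance, with the opposite sign. Take an imbalance of one standard error, s√(2/55), with s = 1.4/√(2(1 − r)).

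| Assumed r | s | One standard error of imbalance | Shift in the contrast | Share of 0.75 |
|---|---|---|---|---|
| 0.3 | 1.18 | 0.226 | 0.158 | 21% |
| 0.5 | 1.40 | 0.267 | 0.133 | 18% |
| 0.7 | 1.81 | 0.345 | 0.103 | 14% |
| 0.9 | 3.13 | 0.597 | 0.060 | 8% |

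**The case against.** **The model may be a summary.** The model is given in one sentence that does not claim to be exhaustive, and covariates are often left to a statistical analysis plan, which is not at hand. This limits how firmly one can say baseline is excluded. Still, the Protocol itself lists the fixed effects, and an analysis plan that follows the list inherits the omission. If that plan already includes baseline, the Protocol needs the same wording.

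**The response may be CDS at every visit, baseline included.** In that case the change would be a contrast within the model. The text allows this reading, since nearby sentences compare visits with baseline. It alters the form of the remedy but does not remove the point.

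**The size is driven by assumptions.** This stands. The correlation is unknown, and averaging twice-daily diary entries could make it high. Equal variances are doubtful on a score with a floor at 0. The power figures come from a t-test at one time point, not from the planned MMRM. They are an illustration, not a forecast.

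**Stronger readings that the Protocol does not support.**
- *Baseline imbalance goes uncorrected, so the estimate is biased.* A change score does subtract baseline. Under equal variances it over-corrects, and over repeated randomizations the estimate is unbiased.
- *The sample size is wrong.* It reproduces exactly for an unadjusted comparison of change.
- *Leaving out hospital is an equal fault, because* "The trial will be conducted at five hospitals in South Korea". No stratification by hospital is stated, so the design as written does not call for that term. No between-hospital variance is given from which a gain could be worked out.

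**Conclusion.** The point holds as an improvement in efficiency, not as an error of validity. The listed primary model omits a baseline value that the schedule already collects, and adjusting for it is generally at least as precise. Under equal variances and an SD of change of 1.4, power at 55 per arm would rise by about 2 to 14 percentage points for r from 0.9 down to 0.3. A baseline imbalance of one standard error would otherwise move the contrast by 0.06 to 0.16 CDS points. If the week-6 variance exceeds the baseline variance, the precision gain can nearly vanish: it is 1% of the variance at k = 1.3 and r = 0.7. No single figure should be quoted as the expected gain. A reader should not infer bias on average, an inflated type I error or a wrong total of 138.

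**What to change.** In the Statistical analysis section, and in the statistical analysis plan if there is one:

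- State whether the modelled response is change from baseline or CDS at each visit.
- If it is change, add baseline CDS and its interaction with visit as fixed covariates in the primary MMRM.
- If baseline is one of the modelled responses, constrain the baseline means to be equal across arms. Baseline should not also be added as a covariate.
- Use the matching baseline value in each secondary MMRM (cough VAS, LCQ-K, GERDQ, HARQ, EQ-5D-5L).
- Hospital as a fixed effect is optional. It would use 4 degrees of freedom, with an unknown gain.

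The cost is wording only, with no new data and no change to the 138. The change should be made before unblinding, because a covariate added afterwards would look chosen to suit the result.
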